## Abstract

**Background:**

Public policy and clinical treatment in tobacco addiction in the UK has focused on cessation: an abrupt attempt to stop all cigarettes. However, recent evidence suggests that allowing more gradual withdrawal from tobacco or even permanent partial substitution by nicotine replacement therapy (NRT) could lead to net benefits to public health. No jurisdiction has introduced smoking reduction programmes in normal clinical care and the best methods for their implementation is uncertain. Community pharmacists offering smoking cessation services in the UK are ideally placed to implement reduction programmes.

This pilot study aims therefore to examine the feasibility of implementing smoking reduction programme in pharmacies, and also to see if behavioural support and a longer treatment affect the success rate for cessation.

**Design and methods:**

This is a 2 × 2 randomised factorial trial of behavioural support versus no support and short versus standard length reduction programme. The pharmacists will recruit 16 patients per pharmacy, 160 smokers altogether. Pharmacists will randomise each participant by sealed envelopes. In a standard supported programme, the pharmacist will give support for 34 weeks, inviting participants to set a treatment goal and providing advice on how to reduce cigarette use. Participants in the short programme will be given the same advice on how to reduce but will reduce smoking over four weeks. Participants in the no support arms will be given a leaflet that describes the reduction programmes in 4-week and 34-week format. All participants are encouraged to use of NRT to support the reduction. These processes will be measured by recording the number of recruited smokers; percentage of those who reduce and sustain their consumption to at least 50% of baseline value, and the proportion of people who attain 4 weeks abstinence and 6 months abstinence. Interviews will assess smokers' and pharmacists' views on the way the programme ran.

**Discussion:**

This is a pilot study to assess the feasibility of offering smoking reduction programme within pharmacies that offer naturalistic setting to show population benefit from these programmes. Findings from this trial will inform the development of evidence-based treatment for smokers who want to reduce and best approaches to engage reluctant quitters onto the programme.

**Trial Registration:**

Current Controlled Trials ISRCTN 2010-019259-24

## Background

Clinical treatment in tobacco addiction has almost exclusively focused on cessation - an abrupt attempt to stop smoking. Some smokers, however, feel that cutting down is an appropriate way to stop smoking. In the English Smoking Toolkit study, 57% of current smokers reported they were cutting down, of whom 26% were using nicotine replacement therapy (NRT) to assist this [1,2]. The UK Department of Health (DH) new tobacco control strategy proposes supporting smokers who feel unable to quit to reduce smoking as a precursor to quitting. No jurisdiction, however, has introduced reduction programmes in normal clinical care.

The evidence that smoking reduction might benefit public health is derived from clinical trials, surveys, and other observational epidemiological data. A systematic review of RCTs and health economic analysis [2,3] found that smoking reduction programmes doubled long-term abstinence rates, with absolute effectiveness only slightly lower than comparable cessation programmes. The cost per quality adjusted life year was less than £2000 for most age groups, rising to less than £5000/QALY for the oldest.

The US guidance, however, recently concluded there was insufficient evidence to recommend smoking reduction programmes [4]. The main concern is that offering reduction alongside cessation programmes will divert smokers from more effective and cheaper cessation programmes to 'easier' but less effective and more expensive reduction programmes. Second, trials of smoking reduction offered free support and medication in countries where such help for smoking cessation is neither widely available nor free and so trials may have inadvertently enrolled smokers keen on cessation rather than reduction and that would have caused the increase in cessation seen in the intervention groups. Third, the trials took place in specialist clinics and drew in highly motivated participants. Consequently the best methods for implementation of reduction programmes outside of such contexts are uncertain and this need to be testedin naturalistic settings to show population benefit from these programmes.

As recognised in Action on Smoking and Health (ASH) guidance to the NHS [5], specialist stop smoking services in the UK do not have the resources necessary to implement smoking reduction programmes. NHS stop smoking service practitioners treat approximately only 30% of all smokers. If the nicotine assisted smoking reduction programmes were to fulfill their potential, up to 5 million smokers might be helped by them. Specialist stop smoking services, however, would not have the workforce to oversee such large numbers of smokers. Therefore the wider primary care workforce might need to help implement reduction programmes.

Community pharmacists are ideally placed to implement reduction programmes. They already provide smoking cessation services as part of the NHS stop smoking service, treating 16% of smokers helped by the NHS in 2008/9. They recruit patients to the service primarily by providing opportunistic brief advice to smokers and therefore they offer a naturalistic setting to test whether reduction programmes can be implemented alongside cessation programmes.

There are no trials investigating whether behavioural support enhances the success of reduction programmes. There are, however, such trials for cessation programmes, which show that behavioural support increases by 50-100% the efficacy of abrupt cessation programmes [6,7]. Industry-sponsored trials of NRT versus placebo provided regular behavioural support and monitoring lasting 15-30 minutes per visit over nine visits [2,3]. Therefore, it is reasonable to believe that reduction programmes work with support, but it is unclear whether support enhances efficacy or whether it is necessary. One study examined the efficacy of NRT versus placebo in smokers that wanted to quit slowly by reduction [8]. Trial participants received no behavioural support. This trial showed a near trebling of long-term abstinence with NRT relative to placebo (OR = 2.86, 95%CI 1.93 to 2.94). These data suggest support might not be necessary. However, although no behavioural support was offered, this study included three visits to assess reduction and cessation, which might motivate adherence to the programme, and hence this might not be a true study of effectiveness of medication without behavioural support. Determining the optimum level of support and monitoring necessary for efficacy in reduction programmes is a priority for NHS implementation.

One NRT industry sponsored trial enrolled participants who did not intend to stop smoking in the next month and randomised them to reduce over one month then stop or to reduce then stop over the typical 6-9 months adopted in the UK [9]. Despite the lack of intuitive fit between participants' intentions and the short programme, the four week reduction programme was more effective than the nine month programme assessed 12 months from the start. For confirmed prolonged reduction, the Mantel-Haenszel relative risk (RR) (95%CI) was 2.69 (1.08-6.68) and for confirmed prolonged abstinence it was 4.57 (1.00-20.93). Shorter and more manageable reduction programmes may be more effective than the standard six-month programme.

We propose to assess by using mixed method approach whether pharmacists can be trained to implement a nicotine assisted reduction programme, how well they do so, and how this is received by smokers and by pharmacists. We also aim to test whether behavioural support adds to the effectiveness of reduction programmes and whether short or standard length programmes are more effective.

### Aims and objectives

#### Aim

To examine the feasibility of introducing nicotine assisted reduction to stop in pharmacies.

To estimate the efficacy of:

• more rapid versus slower reduction programmes

• behavioural support relative to self-help support only.

### Objectives

#### Primary objectives

1) To examine whether pharmacists can be trained to engage smokers who do not want to quit and enrol them in a smoking reduction programme.

2) To compare the relative efficacy of short versus standard length reduction programmes on smoking reduction and smoking cessation.

3) To examine the relative efficacy of supported versus self-guided reduction programmes on smoking reduction and smoking cessation.

#### Secondary objectives

1) To assess which strategies used in enrolment and implementation of the programmes were successful and unsuccessful.

2) To estimate the proportion of smokers enrolled in reduction programmes who reduce successfully.

3) To estimate the proportion of smokers who are referred to cessation programmes and quit successfully.

4) To obtain trial participants' and pharmacists' views on the value of reduction programmes and how such programmes might be improved in future.

## Methods/Design

### Participant Recruitment

Pharmacists who work for NHS stop smoking services will be recruited from areas of high smoking prevalence in Birmingham and Yorkshire region; those treating at least four new smokers for cessation per month will be eligible. Over 60 pharmacists in Birmingham see this many patients in the NHS stop smoking service and most are recruited by brief interventions across the counter, thus providing a naturalistic setting in which to test the implementation of reduction programmes and integration with other smoking cessation efforts.

We plan to recruit 10 pharmacies and for each to recruit four participants into a reduction programme each month, providing a quota of 16 in four months. We plan two waves of recruitment. Using two waves will allow us to learn lessons from the first wave, which is consistent with the developmental nature of this trial.

Educational outreach visits are effective in changing GP's behaviour [10]. We will make visits to local GPs to inform them about the programme and encourage them to refer reluctant quitters to the reduction programme. GPs will be given referral cards for their local pharmacy provider to give to patients. If the recruitment of participants is particularly slow during the either wave, GP's will be asked to send a letter to their registered current smokers. The letter will inform them that the reduction programme is available at their local pharmacy. It will also give details of how they can take part, should they want to, along with an information leaflet about the study.

Pharmacists will be asked to recruit participants opportunistically as well as receiving referrals from GPs. To assist opportunistic recruitment, pharmacists will display a poster in the window. Pharmacists will be compensated for their time with service support funding.

### Training for professionals

Pharmacists will be trained in two evening sessions; attendance to both training sessions is required. In the first session, presentations will be given on principles of the reduction programmes and practicalities of running the trial from recruitment to the final behavioural support visit. The second training session will give pharmacists the opportunity to practice what was learned in the first session by role plays. The pharmacists will be reimbursed for their time of attending to the training. The research team will keep in regular contact with the pharmacy staff and help deal with problems arising during the trial.

### Inclusion criteria

Participants must meet all of the following inclusion criteria:

1) aged 18 years or older.

2) daily smokers with either a CO of at least 10 parts per million (ppm) at least 15 minutes after last smoking or smoke at least 10 cigarettes or 8 g of loose tobacco as "roll up" cigarettes daily.

3) do not intend to stop in the next month, but are prepared to reduce their consumption with any of the programmes offered.

4) evidence of a personally signed and dated informed consent document indicating that the participant has been informed of all pertinent aspects of the study and consents to participate and be randomised to either arm.

5) have either a telephone or email for follow-up.

### Exclusion criteria

There are no contraindications for smokers using NRT. However, there are situations where caution is required. This trial will be conducted with minimal clinical monitoring using treatment regimens that have not been proven to have a population benefit and therefore we have elected to exclude potential participants who have cautions for NRT and this represents the bulk of exclusion criteria. Participants presenting any of the following exclusion criteria will be excluded:

1. currently using other NRT, bupropion, nortriptyline, mecamylamine, reserpine, or varenicline, or undergoing any treatment for tobacco dependence (e.g. acupuncture) that they are not willing to stop using.

2. unstable angina pectoris, myocardial infarction, acute coronary syndrome, or cerebrovascular accident during the last 3 weeks.

3. severe cardiac arrhythmia

4. currently uncontrolled hyperthyroidism

5. active phaeocromocytoma

6. pregnancy, lactation or intended pregnancy in the coming year

7. a severe acute or chronic medical or psychiatric condition or previously diagnosed clinically important renal or hepatic disease, that may increase the risk associated with study participation or may interfere with the interpretation of study results and, in the judgment of the investigator, would make the potential participant inappropriate for entry into this study.

### Withdrawal criteria

Given the established safety profile of NRT, we do not expect any serious adverse events (SAE) and suspected unexpected serious adverse reactions (SUSARs) due to the medication. Nevertheless, pharmacists are required to report in case of any SAE or SUSARs to Principal Investigator. In the event of an SAE or SUSAR that is judged either possibly, probably, or definitely related to NRT, the prescription for NRT will be withdrawn and not re-instituted in that person (Appendix 1).

### Sample size

This is a pilot trial designed to test the processes, examine implementation issues, and reactions to the programme of those involved. We estimated a sample size of 160 participants recruited in 10 pharmacies would be sufficient to test the feasibility of the study. The outcomes therefore include the percentage of pharmacists that agree to participate, the percentage that are trained, the percentage that actually recruit smokers into reduction programmes. Our most important efficacy outcome (because it is linked with unequivocal health benefits) is smoking cessation. We will record the weekly recruitment rate of patients into the reduction programmes and into NHS stop smoking programmes, comparing the rate of recruitment into stop smoking programmes for pharmacists participating in the trial with those not doing so. This will give evidence on whether smokers are being diverted by reduction. For smokers in each type of programme, we will record the number of contacts made, the time of the pharmacist used in delivering the programmes, the amount of NRT used in each arm, the number of people that try to quit, and the number of people that attend the pharmacist for post-cessation support as a proportion of those that try to quit. We will measure the fidelity to each programme by recording some consultations and analysing their content against the schedule of proposed content. We will record sustained smoking reduction and abstinence, although the trial is not powered to detect worthwhile differences in the abstinence outcomes. Four week and six month abstinence rates will be measured following the Russell standard. We will record the proportion of people that complete the webform/telephone follow up.

Any trial to test the role of behavioural support and shorter versus standard length reduction programmes would need to use six month prolonged smoking abstinence as the outcome [11,12]. A sample of 160 participants is not large enough to provide definitive evidence of efficacy with such an outcome because our systematic review showed that standard length programmes lead to about 7% of participants sustaining six month abstinence [13]. However, we assume that shorter reduction programmes are about twice as effective, as suggested by the Haustein trial. Our most important efficacy outcome here is four week abstinence. Based on our systematic review, we expect about 7% of participants who follow the standard length programme with behavioural support to sustain abstinence for six months, which equates to about 21% achieving 4 weeks of abstinence, our main efficacy outcome. Based on this, we get the following table, which shows that this sample size will have 80% power to detect a rate ratio of 1.7 or 90% power to detect a rate ratio of 1.8 (Table 1), lower than observed in Haustein.

**Table 1 T1:** Efficacy of shorter reduction programmes versus standard length

			80% power	90% power
**Base quit proportion**	**RR**	**Quit proportion in intervention**	**N in each arm**	**N in each arm**

0.21	1.7	0.357	146	195

0.21	1.8	0.378	114	152

0.21	1.9	0.399	91	122

The following are also considerations in the sample size. If we take key process measures like attendance for behavioural support sessions as 63% (observed in the review), with 80 smokers receiving behavioural support, we could estimate this with +/-7% precision with 80% confidence. Asking each pharmacy to treat 16 patients, 4 in each arm, will give a reasonable range of experiences for them and us to evaluate the programmes.

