**Figure 1 F1:**
[figure not shown]
**Randomised factorial design trial (2 × 2) of behavioural support versus no support on smoking reduction**.

All participants will receive NRT and be randomised to either behavioural support or no support and either standard length or short reduction; approximately 80 people in each arm.

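### The 21% base rate in Table 1 is given for the supported standard programme but is used for a standard-length group that is about half unsupported; the table's sizes hold only if support has no effect

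*Protocol article*

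**What the plan says.** The Sample size section first gives the rate without mention of support: "our systematic review showed that standard length programmes lead to about 7% of participants sustaining six month abstinence". A few sentences later the planning assumption is tied to support: "we expect about 7% of participants who follow the standard length programme with behavioural support to sustain abstinence for six months". The same sentence turns this six-month figure into the four-week rate of 21% that the plan treats as its main efficacy outcome. Table 1 is built on that 21% and carries the title "Efficacy of shorter reduction programmes versus standard length". From it the text concludes that "this sample size will have 80% power to detect a rate ratio of 1.7 or 90% power to detect a rate ratio of 1.8".

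The design is a 2 × 2 factorial. The Figure 1 legend allocates participants to support or none and to "either standard length or short reduction; approximately 80 people in each arm". The Sample size section plans four participants per cell in each of 10 pharmacies. The No support arms section describes a leaflet in place of advice from the pharmacist.

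On what support does, the Background reports from cessation trials that "behavioural support increases by 50-100% the efficacy of abrupt cessation programmes". It says there are no such trials for reduction programmes and calls the effect there unclear. Of the trials behind the reduction evidence it says: "Industry-sponsored trials of NRT versus placebo provided regular behavioural support and monitoring lasting 15-30 minutes per visit over nine visits".

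**The concern.** The comparison in Table 1 is a factorial main effect. Its control group is everyone allocated to the standard length, supported or not. The rate put into the table is described for the supported part only, and the protocol gives no quit rate for the leaflet part. Using 21% for the whole group amounts to assuming that support makes no difference, which is the question in the third primary objective.

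At a fixed rate ratio, a lower base rate means a larger required sample and lower power. So the table and the power statement drawn from it, both of which concern what the protocol calls its main efficacy outcome, could be too favourable.

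**Working it through.** **Inputs from the protocol.** Base rate 0.21; rate ratios 1.7, 1.8 and 1.9; 80% and 90% power (Sample size, Table 1). About 80 per factor level (Figure 1 legend). Cell size 4 × 10 = 40 (Sample size). Gain from support of 50-100%, abrupt cessation only (Background).

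**Assumptions.** Two-sided 5% test, which the section does not state but which reproduces the table. Equal allocation, no allowance for pharmacy clustering, and the same short-versus-standard rate ratio with and without support.

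**Formulas.** With p̄ = (p1 + p2)/2:

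- n per arm = [1.960 √(2p̄(1−p̄)) + z √(p1(1−p1) + p2(1−p2))]² / (p2−p1)², where z = 0.842 for 80% power and 1.282 for 90%
- power at n per arm = Φ{ [(p2−p1)√n − 1.960 √(2p̄(1−p̄))] / √(p1(1−p1) + p2(1−p2)) }

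**1. Reproducing Table 1.** For p1 = 0.21 and p2 = 0.357: (1.2492 + 0.5293)² / 0.147² = 146.4; the table has 146. All six entries follow in the same way: 146.4/195.5, 114.3/152.5 and 91.9/122.5, against 146/195, 114/152 and 91/122. The table is this formula rounded down.

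**2. Rate for the whole standard-length group.** If support multiplies the quit rate by f, the unsupported rate is 0.21/f, and with 40 in each half the group rate is (0.21 + 0.21/f)/2.

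- f = 1 (no effect): 0.21
- f = 1.5: (0.21 + 0.14)/2 = 0.175
- f = 2: (0.21 + 0.105)/2 = 0.1575

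**3. Required n per arm and power at 80 per level.** For example, at base 0.175 and rate ratio 1.7, p2 = 0.2975 and n = (1.1774 + 0.5003)² / 0.1225² = 187.6. At base 0.1575, p2 = 0.26775 and n = (1.1341 + 0.4826)² / 0.11025² = 215.0. For power at base 0.175: (0.1225 × 8.944 − 1.1774)/0.5944 = −0.137, and Φ(−0.137) = 0.445.

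| Base rate | Rate ratio | n, 80% power | n, 90% power | Power at 80 per level |
|---|---|---|---|---|
| 0.21 | 1.7 | 146.4 | 195.5 | 54% |
| 0.21 | 1.8 | 114.3 | 152.5 | 65% |
| 0.21 | 1.9 | 91.9 | 122.5 | 74% |
| 0.175 | 1.7 | 187.6 | 250.6 | 45% |
| 0.175 | 1.8 | 147.0 | 196.2 | 54% |
| 0.175 | 1.9 | 118.6 | 158.3 | 63% |
| 0.1575 | 1.7 | 215.0 | 287.4 | 40% |
| 0.1575 | 1.8 | 168.8 | 225.4 | 49% |
| 0.1575 | 1.9 | 136.5 | 182.2 | 57% |

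Relative to the 0.21 base, n rises by 28% (187.6/146.4) to 49% (182.2/122.5). A weaker, assumed gain of 25% gives a group rate of 0.189 and n of about 170 for rate ratio 1.7 at 80% power.

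**4. The other reading.** If Table 1 was meant for the supported cells alone, 21% is the right input, but only about 40 per arm are available. Power is then 31% at 1.7 and 38% at 1.8.

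**The case against.** The strongest reply is that the documents do not say support works in reduction programmes. The Background calls this unclear. It also cites a trial of NRT against placebo without behavioural support that still showed a near trebling of abstinence, and says this suggests support might not be needed. The 50-100% gain comes from abrupt cessation. This reply stands as a limit on the conclusion. A reader might infer that the required sizes are simply understated, and the documents do not support that: with no effect of support, every entry in Table 1 is unchanged. It does not remove the mismatch. The placebo comparison does not estimate the effect of support, and the Background concedes that its three assessment visits may have helped adherence.

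A second reply is that the 7% is also stated for standard-length programmes in general. But the Background says the industry trials gave regular support over nine visits, and the sentence from which Table 1 is derived names support explicitly.

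A third is that little hangs on the table: the Sample size section justifies 160 on feasibility and says the trial is not powered for worthwhile differences in abstinence. That limits the importance of the point. The same section nevertheless goes on to claim 80% and 90% power.

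A reader might also infer that the 21% will be carried into the definitive trial. The Data analyses section says that updated estimates will set that trial's size, so this is not supported.

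**Conclusion.** The point holds as a mismatched input, not as an arithmetic slip. Table 1 is correct for a 21% base, but that base is described for about 40 supported people and applied to about 80, half of them unsupported.

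The size of the effect is conditional. It is nil if support has no effect. If support works as the protocol reports for abrupt cessation, the base is 15.8-17.5%, required numbers rise by about 28-49%, and power at 80 per level is 40-45% (rate ratio 1.7) or 49-54% (1.8). These figures rest on the assumptions listed with the calculation, chiefly that the cessation gain carries over and that the two factors do not interact.

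One part does not depend on the effect of support. The stated 80% and 90% power are not delivered on any reading: 54% and 65% at a 21% base with 80 per level, and 31% and 38% if only the supported cells are meant. That larger shortfall arises because Table 1 needs 146 and 152 in each arm, against about 80 available. Correcting only that would leave the base-rate question open.

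**What to change.** In the Sample size section, state the four-week quit rate assumed without support, or a range that includes no effect. Show Table 1 at standard-length base rates of about 0.16, 0.175 and 0.21, with the support effect assumed for each. Replace the 80%/90% power statement with the power at 80 per factor level, for example 54% at rate ratio 1.7 and 65% at 1.8 for a 21% base, with the lower values beside them.

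The cost is a recalculated table and a few sentences. The figures become less favourable, but the 160 rests on feasibility, so no further participants and no change in design are needed.

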#### Behavioural intervention

This is a 2 × 2 randomised factorial design trial of behavioural support versus no support and short versus standard length reduction programme (Figure 1). It is a pilot study for a later definitive trial.

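### The stated 80% and 90% power needs about 150 people per programme length; the trial has 80, giving about 54% at RR 1.7 and 65% at RR 1.8

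*Protocol article*

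**What the plan says.** The Sample size section first rests the number on feasibility: "We estimated a sample size of 160 participants recruited in 10 pharmacies would be sufficient to test the feasibility of the study". It adds that "the trial is not powered to detect worthwhile differences in the abstinence outcomes", and the next sentence names both four-week and six-month abstinence.

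The same section then makes four-week abstinence the main efficacy outcome. It takes 21% as the expected rate on the standard programme with support and presents Table 1 for short versus standard length. From that table it concludes that "this sample size will have 80% power to detect a rate ratio of 1.7 or 90% power to detect a rate ratio of 1.8", and remarks that these ratios are smaller than the one seen in the cited trial of short versus standard reduction.

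The size of each comparison group is stated elsewhere:
- Behavioural intervention section: "This is a 2 × 2 randomised factorial design trial of behavioural support versus no support and short versus standard length reduction programme".
- Figure 1 legend: "either standard length or short reduction; approximately 80 people in each arm".
- Sample size section, on precision of attendance: "with 80 smokers receiving behavioural support".
- Sample size section, on pharmacy quotas: "Asking each pharmacy to treat 16 patients, 4 in each arm".

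**The concern.** The sample size columns of Table 1 are headed as numbers per arm, yet the sentence that cites the table applies it to a trial of 160 people in total. Only 80 of them are at each level of the programme-length factor. The two cells that match the claim, 146 and 152, both lie just under 160, so the total appears to have been read as a per-arm size.

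Short versus standard length on cessation is primary objective 2, and four-week abstinence is the outcome on which that comparison is sized. If the trial finds no difference, a reader relying on the stated 80% to 90% power would take this as fair evidence against an RR of 1.7 or 1.8. The results are also meant to inform a definitive trial, so a wrong impression of what this one could detect would carry forward.

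**Working it through.** **Inputs**
- Total: 160 (Abstract; Sample size).
- Allocation: 10 pharmacies × 4 per cell = 40 per cell, so 80 at each level of each factor. This agrees with the Figure 1 legend and with the count of supported smokers.
- Base rate 0.21; comparison rates 0.357 (RR 1.7), 0.378 (RR 1.8), 0.399 (RR 1.9) (Table 1).
- Significance level: not stated for this calculation. Two-sided 5% is assumed. It fits the planned 95% confidence intervals and reproduces Table 1. One-sided 5% does not: it gives 116 and 160 for RR 1.7, against the stated 146 and 195.
- Dropout: no inflation, because all randomised participants stay in the denominator (Data analyses).

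**Step 1. Reproduce Table 1.** With d = p2 − p1 and p̄ = (p1 + p2)/2,

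n per arm = [1.96·√(2p̄(1−p̄)) + z_power·√(p1(1−p1) + p2(1−p2))]² / d²

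- RR 1.7, 80%: d = 0.147, p̄ = 0.2835; (1.96 × 0.6374 + 0.8416 × 0.6288)² / 0.0216 = 146.4.
- RR 1.8, 90%: d = 0.168, p̄ = 0.294; (1.96 × 0.6443 + 1.2816 × 0.6333)² / 0.0282 = 152.5.

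| RR | 80%: computed (Table 1) | 90%: computed (Table 1) |
|---|---|---|
| 1.7 | 146.4 (146) | 195.5 (195) |
| 1.8 | 114.3 (114) | 152.5 (152) |
| 1.9 | 91.9 (91) | 122.5 (122) |

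All six entries match once the decimals are dropped. The table is therefore correct as numbers per arm. The totals behind the claim are 2 × 146 = 292 and 2 × 152 = 304.

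**Step 2. Power at 80 v 80.** The same formula solved for power:

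power = Φ{ [d√n − 1.96·√(2p̄(1−p̄))] / √(p1(1−p1) + p2(1−p2)) }

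- RR 1.7: (0.147 × 8.944 − 1.2492) / 0.6288 = 0.104, so power = 54.2%.
- RR 1.8: (0.168 × 8.944 − 1.2628) / 0.6333 = 0.379, so power = 64.8%.
- RR 1.9: 74.3%. RR 2.0: 82.2%.

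Solving for the RR at n = 80 gives 1.97 for 80% power and 2.13 for 90%.

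**Step 3. Could another method rescue the claim?** Power at 80 v 80:

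| Method | RR 1.7 | RR 1.8 |
|---|---|---|
| Unpooled variance | 55.2% | 66.0% |
| Arcsine | 54.7% | 65.3% |
| Exact power of the chi-square test | 55.0% | 65.6% |
| Chi-square with continuity correction | 47.4% | 58.4% |
| One-sided 5% | 66.4% | 75.8% |
| Two-sided 20% | 78.6% | 85.8% |
| One-sided 20% | 89.2% | 93.5% |

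None gives 80% and 90% together. With 160 v 160 at two-sided 5%, power would be 83.4% and 91.3%. That is consistent with the total having been used as the arm size.

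**Step 4. Precision.** At 21% v 35.7% with 80 per group, the 95% confidence interval for the risk difference has half-width 1.96 × √(0.3955/80) = 13.8 percentage points.

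**The case against.** The strongest defence is that little depends on the sentence. This is a pilot, its size is justified by feasibility, and the same section says that 160 cannot give definitive evidence on six-month abstinence and disclaims power for abstinence. The Data analyses section plans risk differences with 95% confidence intervals and names no test for the efficacy outcomes, so part of the remedy is already in place. All of this limits the harm. It does not make the figures true. The disclaimer leaves two statements in one section that conflict; if it is read as covering six months only, the conflict goes but the false power figures remain.

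A second point is that the protocol assumes a roughly twofold effect, for which 80 per level gives about 82% power at the 21% base rate. That stands, and the design is not shown to be inadequate for that effect. What is lost is the margin that the protocol claims. The RR detectable with 80% power, 1.97, is practically the assumed effect, and the RR for 90% power, 2.13, exceeds it.

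A third is that 54% and 65% are themselves conditional. They need two-sided 5%, and they apply a 21% base rate, given for the supported standard programme, to a group half of which has no support. This is fair, but it points the other way. If the pooled base rate were 17.5% (an assumption for illustration), power would be about 45% and 54%.

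Finally, the claim concerns programme length only. No power is stated for supported versus self-guided reduction, although that comparison also has 80 per level.

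**Conclusion.** The power statement is wrong as written. With 80 people per programme length, a 21% base rate and a two-sided 5% test, power is about 54% rather than 80% at RR 1.7, and about 65% rather than 90% at RR 1.8. The stated power would take 292 and 304 participants in total.

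That the claim fails needs no assumption about the significance level: the smallest entry in Table 1 is 91 per arm, and the protocol gives 80. The exact replacement figures do rest on two-sided 5% and the 21% base rate. Like Table 1, they ignore any pharmacy effect. That the total was taken for the arm size is an inference, though a likely one.

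**What to change.** Replace the power sentence in the Sample size section. Suggested text: *With 80 participants on each programme length, a four-week abstinence rate of 21% on the standard programme and a two-sided 5% level, the trial has about 54% power for a rate ratio of 1.7, 65% for 1.8 and 82% for 2.0; 80% and 90% power are reached at rate ratios of about 1.97 and 2.13.* Add that power is lower if the base rate, averaged over supported and unsupported participants, is below 21%.

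Then:
- Keep Table 1, and say beside it that the trial provides 80 per arm, fewer than any entry.
- Make the text agree with the disclaimer of power for the abstinence outcomes, and say whether that disclaimer covers four-week abstinence.
- Remove or reword the remark that the detectable ratios lie below the one seen in the cited trial, since it was made for 1.7 and 1.8.
- State that efficacy results are to be read as estimates with 95% confidence intervals, with a half-width of about 14 percentage points at 21% v 35.7%. The Data analyses section already plans these intervals.

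The cost is wording only, with no extra participants and no change to conduct or analysis. The stated power becomes less favourable.
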